# Nutritional support and prophylaxis of azithromycin for pregnant women to improve birth outcomes in peri-urban slums of Karachi, Pakistan—a protocol of multi-arm assessor-blinded randomized controlled trial (Mumta PW trial)

**DOI:** 10.1186/s13063-021-05960-9

**Published:** 2022-01-03

## Abstract

**Background:**

Maternal undernutrition is critical in the etiology of poor perinatal outcomes and accounts for 20% of small-for-gestational-age (SGA) births. High levels of food insecurity, antenatal undernourishment, and childhood undernutrition necessitate the supplementation of fortified balanced energy protein (BEP) during pregnancy in low-income settings especially with scarce literature available in this subject. Hence, this paper extensively covers the protocol of such a trial conducted in an urban slum of Karachi, Pakistan.

**Methods:**

The trial is community-based, open-labelled, four-arm, and randomized controlled that will include parallel group assignments with a 1:1:1:1 allocation ratio in low-income squatter settlements in urban Karachi, Pakistan. All pregnant women (PW), if identified between > 8 and < 19 weeks of gestation based on ultrasound, will be offered routine antenatal care (ANC) counseling and voluntary participation in the trial after written informed consent. A total number of 1836 PW will be enrolled with informed consent and randomly allocated to one of the four arms receiving: (1) ANC counseling only (control group), (2) ANC counseling plus BEP supplement (intervention arm 1), (3) ANC counseling plus BEP supplement plus 2 doses azithromycin (intervention arm 2), or (4) ANC counseling plus BEP supplement plus daily single dose of nicotinamide and choline (intervention arm 3).

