## Methods

### Trial design

This is a multi-arm community-based randomized controlled, open-label, assessor-blinded superiority trial with a treatment allocation ratio of 1:1:1:1. A multi-arm trial was selected to determine the incremental impact of BEP to the pregnant woman, along with two doses of oral azithromycin or oral daily nicotinamide and choline on birth weight. This protocol has been developed in accordance with the guidelines set forth by Standard Protocol Items: Recommendations for Interventional Trials (SPIRIT) [26].

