### Sample size

The sample size is calculated via permutation and subsequent adjustment for three comparisons between arms, i.e., intervention arms with control. Improved perinatal outcomes are hypothesized with the supplement of BEP alone or co-administration of BEP supplement with azithromycin as well as with nicotinamide and choline. Thus, the sample size estimated per arm is based on 1-tailed hypothesis testing of birth weight as the primary outcome, a significance level of 2.5% to account for multiple comparisons, and initial assumption of dropout proportion of 21% of study participants assumed in the trial. For birth weight (the primary outcome), it is assumed that the mean difference will be at least 100 g [30]. In order to achieve a test power of 80% and maintain family-wise error rate (FWER) of 0.05; Bonferroni method for three comparisons, alpha of 0.017, and an estimated sample size of 370 pregnant women per arm was attained. A 21% dropout rate was thereafter considered on account of miscarriages, stillbirths, early neonatal deaths, losses to follow-ups, and missed birth assessments due to varying on-field challenges owing to the pandemic. Hence, the sample size was thereafter adjusted to 471 pregnant women in each arm making up a total of 1884 pregnant women for this trial.

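### The abstract gives a total enrolment of 1836, but the sample-size section derives 1884; the 1836 has no derivation and falls short of the plan's own 370 evaluable women per arm.

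*Protocol article*

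**What the plan says.** The Methods paragraph of the abstract gives the planned total: "A total number of 1836 PW will be enrolled with informed consent and randomly allocated to one of the four arms".

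The Sample size section builds its figure in steps. The assumed effect on birth weight is stated as "it is assumed that the mean difference will be at least 100 g". The aim is to "achieve a test power of 80% and maintain family-wise error rate (FWER) of 0.05", with a Bonferroni alpha of 0.017 for three comparisons, and on that basis "an estimated sample size of 370 pregnant women per arm was attained". Losses are then allowed for: "A 21% dropout rate was thereafter considered on account of miscarriages, stillbirths, early neonatal deaths, losses to follow-ups". The section ends: "the sample size was thereafter adjusted to 471 pregnant women in each arm making up a total of 1884 pregnant women for this trial".

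Trial design describes a "superiority trial with a treatment allocation ratio of 1:1:1:1", so either total divides equally over four arms.

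Trial status names version 1.6 of 9 October 2021 as the active protocol. Table 3 lists that version as a recalculation of the sample size for multiple-arm comparison, and version 1.5 as an increase for new dropout rates. Recruitment was ongoing and expected to finish in January 2022. The article was published on 3 January 2022.

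**The concern.** Both figures stand in the current text, and each is given as the single planned total for the same trial. A reader who takes the target from the abstract gets 459 women per arm; a reader who takes it from the Sample size section gets 471.

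This matters in two ways. First, recruitment was close to its end when the article appeared, so the question of whether the trial met its planned size would soon be asked, and the answer depends on which figure is used. Second, 1836 is not just a different number: combined with the article's own dropout rate, it does not deliver the evaluable number to which the article ties its 80% power.

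**Working it through.** **Inputs.** From the Sample size section: 370 evaluable per arm, 21% dropout, 471 per arm, 1884 in total, difference 100 g, power 80%, Bonferroni alpha 0.017. The same section also mentions one-tailed testing at 2.5%. From the abstract: 1836 in total. From Trial design: four arms, 1:1:1:1. No standard deviation is stated.

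**Step 1: reproduce the plan's own figure.** Inflation for dropout is n / (1 − d).
- With d taken as exactly 21%: 370 / 0.79 = 468.4, rounded up to 469. The stated 471 is 2 women higher (0.4%).
- Dropout implied by 471: 1 − 370/471 = 21.4%, which is 21% as a whole per cent.
- With 21% read as anything from 20.5% to 21.5%, the result runs from 370 / 0.795 = 465.4 to 370 / 0.785 = 471.3, and 471 lies inside.
- Total: 4 × 471 = 1884, exact.

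The chain 370 → 471 → 1884 therefore reproduces within rounding.

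**Step 2: put the abstract's figure through the same chain.**
- Per arm: 1836 / 4 = 459.
- Gap to the Sample size section: 471 − 459 = 12 per arm; 1884 − 1836 = 48 in total, or 48/1884 = 2.5%.
- Evaluable at 21% dropout: 459 × 0.79 = 362.6, about 363, against 370 required.
- Dropout at which 459 still gives 370: 1 − 370/459 = 19.4%.

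So 1836 does not round to the same answer. It needs a dropout rate about 1.6 percentage points below the one stated.

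**Step 3: effect on power.** Because no standard deviation is given, it has to be assumed. I take the value at which 370 per arm gives exactly 80% power for 100 g (normal approximation):

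SD = 100 / [√(2/370) × (z_alpha + z_0.80)].

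Power at 362.6 evaluable per arm is then Φ[√(362.6/370) × (z_alpha + z_0.80) − z_alpha], with √(362.6/370) = 0.990 and z_0.80 = 0.842. The text leaves the sidedness and level open to more than one reading, so three are shown.

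| Reading of alpha | z_alpha | Implied SD | Power at 362.6 per arm |
|---|---|---|---|
| 0.017 one-sided | 2.120 | 459 g | 79.2% |
| 0.017 two-sided | 2.387 | 421 g | 79.1% |
| 0.025 one-sided | 1.960 | 485 g | 79.2% |

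For comparison, 471 per arm leaves 471 × 0.79 = 372.1 evaluable and about 80.2% power on each reading. The shortfall from 1836 is about one percentage point, whichever reading is taken.

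**The case against.** The strongest reply is that the article shows which figure has support. The Sample size section gives one chain ending in 1884. It adjusts for three comparisons, which fits the recalculation for multiple-arm comparison that Table 3 records under the active version 1.6. The figure 1836 appears only in the abstract and has no derivation. Nothing suggests that recruitment is run from the abstract, the gap is 2.5%, and the power cost is about one point.

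Most of this stands, and it limits the point. A reader might infer that the planned size is not fixed at all. The documents do not support that: there is one derived target and one unsupported figure, not two rival plans. A reader might also infer that 471 does not follow from 370 and 21%, or that the two come from different calculations. That fails too: the gap is 2 women, and an unrounded dropout near 21.4% closes it.

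What the reply does not remove is the contradiction. The abstract is current text, not an amendment log. It may carry a figure from before the last revision, but the article does not say so, and a left-over total in current text would still need correcting.

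**Conclusion.** The point holds as an internal contradiction in a headline design figure: 1836 in the abstract against 1884 in the Sample size section, a difference of 48 women. At the article's own dropout rate, 1836 yields about 363 evaluable women per arm instead of 370. That part rests only on figures in the document.

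The power figure of about 79% rests on an assumed standard deviation (421 to 485 g, back-calculated from 370 per arm), since none is stated. The practical loss is small. The reason to act is that the planned total is stated two ways at a time when recruitment was about to close. The derivation of 471 and 1884 is sound within rounding.

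**What to change.** State one total everywhere.

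- If 1884 is the target of the active version 1.6, change the abstract from 1836 to 1884.
- If recruitment is to stop at 1836, change the Sample size section to 459 per arm, about 363 evaluable per arm at 21% dropout, and power of about 79%, and give the standard deviation on which that power rests.

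Optionally, give the dropout rate to one decimal, so that the step from 370 to 471 can be followed exactly.

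The cost is a wording correction in one or two places, carried to any other document that quotes the target. The first option needs no change to design or analysis; the second puts on record a slightly smaller trial.

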**Trial registration:**

ClinicalTrials.govNCT04012177. Registered on July 9, 2019.

## Background

Suboptimal nutrition during pregnancy may compromise maternal health, birth outcomes, and offspring development [1, 2]. Undernourishment in utero can stress the developing fetus and adversely reprogram its evolving phenotype [3]. Growth-restricted fetuses are thereafter predisposed to several perinatal health risks [4] including intrauterine growth retardation (IUGR), preterm delivery [5], low birth weight (LBW), immunocompromised status, childhood stunting, and neurocognitive deficits in addition to fetal, maternal, and infant mortality [6–8]. Hence, maternal undernutrition poses a significant global health burden [9], accounting for 7% morbidity [10] plus 70% neonatal [11] and 20% maternal [10] mortality rates worldwide. This situation is even more dismal for resource-constrained and food-insecure countries like Pakistan, where 18% of married women of reproductive age are nutrient-deficient, and thus 44% of children have stunted growth [12].

Maternal undernutrition is, in fact, a significant determinant of LBW in developing countries [13]. An indicator to measure LBW is small-for-gestational-age (SGA), defined as birth weight below the 10th percentile of optimal weight for a given gestational age and sex of a population subset [14]. Of the 23.3 million SGA births globally [15], around 20% are attributable to maternal undernutrition during pregnancy [16]. To address this, the World Health Organization Antenatal Care (WHO-ANC) guidelines recommend the use of fortified balanced energy protein (BEP) supplements during pregnancy to reduce the risk of stillbirth and SGA birth [17]. Following this recommendation, compositional guidance for a ready-to-use supplementary food (RUSF) for pregnant women was developed by the Bill and Melinda Gates Foundation (BMGF) in 2016 [18].

Additionally, the use of prophylactic antibiotics and micronutrients along with BEP supplements have shown to improve perinatal outcomes when used solitarily in various maternal nutritional interventions across low- and middle-income populations [19–21]. For instance, the incidence of preterm delivery and LBW is noted to reduce when two azithromycin doses are administered as a preventive measure for maternal reproductive tract infections [22]. Similarly, a higher maternal choline intake, an essential micronutrient for neurogenesis [23], reportedly improves fetal neurocognitive development [24]. Lastly, dietary supplementation with vitamin B3 or nicotinamide may protect against retarded linear growth in children, as suggested by a recent cohort study [25].

Although substantial data on solitary administration of macro- and micro-nutritional supplements and antimicrobial prophylaxis during pregnancy exists, there is a need for further exploration of the efficacy and synergistic role of these micro- and macro-ingredients on pregnant women (PW) when administered concomitantly. In the context of Pakistan, recent experience with such ready-to-use supplements has been limited. Also, in many cases, these products’ acceptability, efficacy, and effectiveness have not been adequately studied to understand the circumstantial needs. Our study aims to fulfill this lacuna by evaluating and comparing the efficacy of fortified, balanced energy protein (BEP) supplements in malnourished PW from impoverished settings. This will be coupled with or without two prophylactic doses of oral azithromycin and micronutrient fortification with nicotinamide and choline.

### Objectives

The primary objective is to compare the efficacy of fortified, balanced energy protein (BEP) supplements in pregnant women (intervention arm 1) administered solitarily, or in combination with two prophylactic dose of oral azithromycin at weeks 20 and 28 of pregnancy (intervention arm 2), or in combination with daily oral supplements of nicotinamide and choline (intervention arm 3) with that of standard antenatal care (ANC) versus nutritional counseling alone (control arm) in improving the birth weight assessed less than 72 h of birth. The secondary objective is to compare the impact of the interventions on birth length and other anthropometric measurements of the newborn and mother at birth. Further, blood and stool biomarkers of the subjects will be assessed during pregnancy while cord blood, breast milk, and colostrum will be collected at birth. During extended follow-ups from 0 to 11 months, mother-infant dyad will be assessed for anthropometry, and blood and stool specimens will be collected periodically from the sub-sample of the dyad.

## Methods

### Trial design

This is a multi-arm community-based randomized controlled, open-label, assessor-blinded superiority trial with a treatment allocation ratio of 1:1:1:1. A multi-arm trial was selected to determine the incremental impact of BEP to the pregnant woman, along with two doses of oral azithromycin or oral daily nicotinamide and choline on birth weight. This protocol has been developed in accordance with the guidelines set forth by Standard Protocol Items: Recommendations for Interventional Trials (SPIRIT) [26].

### Study setting

The trial will be conducted at Rehri Goth, an impoverished peri-urban coastal slum located along the Arabian Sea belt in the Malir District of Karachi, Pakistan. This ancient site comprises of Sindhi and Baloch ethnicities and a predominant Islamic religion with high illiteracy rate. With approximately 59,000 residents based on a 2017 census, this site has an annual birth rate of around 1500 per year and a cohort of 22% child-bearing-aged female and 3.6% infant population [27]. There are 25 clinics in the area with only one qualified (MBBS) doctor, one government out-patient health center and no maternity home. The lady health workers serving the site belong to Agha Khan Health Services. Major diseases prevalent are diabetes mellitus, skin disorders, and hepatitis [28]. The main occupation in the village is fishing, which is seasonal and yields low income due to unfavorable weather conditions and law restrictions. Seasonal rainfall results in flooding and increases the risk of enteric infections [29]. In the target population, around 27% of pregnant women are malnourished, while about 54% are anemic and approximately 20% of babies are born with low birth weight, according to unpublished data from the VITAL Pakistan Trust (VPT). Thus, Rehri Goth has been a significant focus of VPT operations in tandem with the Aga Khan University Hospital (AKUH) as its partner organization.

### Study population and eligibility

Pregnant women between 13 and 49 years of age will be enrolled if they fulfill the inclusion and exclusion criteria provided in Table 1. New pregnancies in the catchment area are usually identified during routine surveillance rounds and referred to the ANC clinic of VPT. Women with gestational age between > 8 and < 19 weeks based on ultrasound will be screened for eligibility by the research trial team onsite. For eligible participants, written informed consent will be obtained in the local language before they are enrolled for the trial.

**Table 1 Tab1:** Inclusion and exclusion criteria

Inclusion	Exclusion
▪ Gestational age of 8 to 19 weeks confirmed by ultrasound ▪ A resident of the area for at least the last six months. ▪ Willing to spend the whole pregnancy duration after enrollment ▪ Singleton and viable fetus on ultrasound ▪ Not working and available for ANC and follow-up visits at home ▪ Previously not enrolled in pregnant and lactating women trials	▪ Pregnant women with mid-upper arm circumference (MUAC) ≥ 30.5 cm ▪ Known food allergies

### Sample size

The sample size is calculated via permutation and subsequent adjustment for three comparisons between arms, i.e., intervention arms with control. Improved perinatal outcomes are hypothesized with the supplement of BEP alone or co-administration of BEP supplement with azithromycin as well as with nicotinamide and choline. Thus, the sample size estimated per arm is based on 1-tailed hypothesis testing of birth weight as the primary outcome, a significance level of 2.5% to account for multiple comparisons, and initial assumption of dropout proportion of 21% of study participants assumed in the trial. For birth weight (the primary outcome), it is assumed that the mean difference will be at least 100 g [30]. In order to achieve a test power of 80% and maintain family-wise error rate (FWER) of 0.05; Bonferroni method for three comparisons, alpha of 0.017, and an estimated sample size of 370 pregnant women per arm was attained. A 21% dropout rate was thereafter considered on account of miscarriages, stillbirths, early neonatal deaths, losses to follow-ups, and missed birth assessments due to varying on-field challenges owing to the pandemic. Hence, the sample size was thereafter adjusted to 471 pregnant women in each arm making up a total of 1884 pregnant women for this trial.

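### The sample-size section gives two different multiplicity-adjusted levels for each birth-weight comparison, and the one-tailed 2.5% does not hold the stated family-wise error rate of 0.05

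*Protocol article*

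**What the plan says.** The Sample size section names three comparisons, each intervention arm against control, and describes the calculation as "1-tailed hypothesis testing of birth weight as the primary outcome, a significance level of 2.5% to account for multiple comparisons". Two sentences later, in giving the 80% power, it sets out to "maintain family-wise error rate (FWER) of 0.05; Bonferroni method for three comparisons, alpha of 0.017, and an estimated sample size of 370 pregnant women" in each arm. The assumed effect is given as follows: "it is assumed that the mean difference will be at least 100 g". No SD of birth weight appears anywhere in the article, and the sidedness of the 0.017 is not repeated.

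No other section settles the level. Statistical analysis names one-way ANOVA with baseline adjustment and the superiority principle, but gives neither an alpha nor a sidedness. Table 3 under Trial status records that version 1.6 recalculated the sample size for multiple-arm comparison, but it does not say which level was dropped or kept.

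**The concern.** Two different numbers are offered as the level that already allows for multiplicity. The 2.5% cannot be rescued by reading it as the family-wise level, because the section states that as 0.05; a 2.5% family split over three tests would need 0.025/3 = 0.0083 each.

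At stake is the threshold for three efficacy claims on the only primary outcome. A one-sided p-value of 0.02 for one arm against control is positive under the 2.5% sentence and negative under a 0.017 rule. If the text keeps both, the protocol does not prevent the more favourable one from being cited once results are known. The quoted 80% power also belongs to whichever level was actually used to reach 370, and the text does not show which that was.

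**Working it through.** **Inputs (Sample size, except where noted).** Difference 100 g; power 80%; 370 evaluable women per arm; FWER 0.05; three comparisons ("adjustment for three comparisons between arms, i.e., intervention arms with control"); levels 0.025 one-tailed and 0.017 with sidedness not restated; equal allocation ("treatment allocation ratio of 1:1:1:1", Trial design). The SD is not stated, so 370 cannot be reproduced directly. It is solved for below and shown as a range.

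**Step 1. Which figures agree?**

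- 0.05/3 = 0.01667, which rounds to 0.017. The Bonferroni level and the FWER therefore agree up to rounding (3 × 0.017 = 0.051).
- 3 × 0.025 = 0.075, which exceeds 0.05.

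**Step 2. FWER actually delivered.** With equal arms and a shared control, the three test statistics have pairwise correlation 0.5. The last column comes from simulating them with 3 million draws.

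| Level for each of three tests | Bonferroni bound | If independent, 1 − (1 − α)³ | Shared control |
|---|---|---|---|
| One-sided 0.025 | 0.075 | 0.073 | 0.063 |
| One-sided 0.017 | 0.051 | 0.050 | 0.044 |
| Two-sided 0.017 | 0.051 | 0.050 | 0.046 |

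The 2.5% level exceeds 0.05 on every calculation. With the shared control, 0.017 stays below 0.05 whether one- or two-sided.

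**Step 3. SD implied by 370 per arm.** By the normal approximation, SD = 100 × √(370/2) / (z_α + z_0.80), with √185 = 13.601 and z_0.80 = 0.8416.

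| Level used for sizing | z_α | Implied SD |
|---|---|---|
| One-sided 0.025 | 1.960 | 1360.1 / 2.802 = 485.5 g |
| One-sided 0.017 | 2.120 | 1360.1 / 2.962 = 459.2 g |
| Two-sided 0.017 | 2.387 | 1360.1 / 3.228 = 421.3 g |

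Each is arithmetically possible, so the figure of 370 does not reveal its level.

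**Step 4. Power when the sizing level and the testing level differ.** Power = Φ(100 / (SD × √(2/370)) − z_α).

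- Sized at one-sided 0.025 (SD 485.5 g), tested at one-sided 0.017: Φ(2.802 − 2.120) = Φ(0.682) = 75.2%. At exactly 0.05/3 it is 75.0%.
- Sized and tested at one-sided 0.017 (SD 459.2 g): 80%, with FWER about 0.044.
- Sized and tested at two-sided 0.017 (SD 421.3 g): 80%, with FWER about 0.046.
- Sized at one-sided 0.017, tested at one-sided 0.025: 84.2%, but with FWER about 0.063.

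The stated power and FWER therefore hold together whenever 0.017 was used, with the same sidedness, for both sizing and testing. Within the levels the document names, and keeping the test one-sided, the worst case for power is about 75%.

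**The case against.** The strongest reply is that one sentence ties everything together: 80% power, FWER 0.05, Bonferroni, 0.017 and 370 per arm. That sentence is consistent in itself, and Table 3 makes it plausible that the 2.5% is a remnant of an earlier version. It is also true that a decision threshold often sits in the statistical analysis plan, and that a journal article may leave the SD to the full protocol. Most of this stands. It shows that 0.017 is probably the intended level, and that the missing SD is no fault in itself. It does not remove the 2.5% from the current text, where it is expressly offered as the multiplicity allowance.

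Two stronger readings are tempting, and the document supports neither.

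- A reader might infer that all three error rates clash, so that 80% power and FWER control cannot both hold. They can: 0.017 and 0.05 agree, and an SD of about 459 g (one-sided) or 421 g (two-sided) gives 80% power at 370 per arm.
- A reader might infer that true power is only about 66% to 72%. Those are the values at two-sided 0.0167 if 370 was sized one-sided (65.8% with SD 485.5 g, 71.5% with SD 459.2 g). The only sidedness the article states is one-tailed, so this shortfall comes from substituting a test that the article does not specify. In the same way, objecting that one-sided 0.0167 tests place the whole 5% on the benefit side states a preference about convention and identifies no contradiction.

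**Conclusion.** Wrong as written. The section gives two incompatible levels for each comparison, and the one-tailed 2.5% does not do what the text says it does: it yields an FWER of about 6.3% with a shared control (bound 7.5%) against the stated 0.05. The 0.017 is sound.

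A loss of power is possible but not shown. It is about five percentage points (75% against 80%) if 370 was sized at one-sided 2.5% and tested at one-sided 0.017, and nil if 0.017 was used consistently. These figures assume pairwise comparisons of means by the normal approximation, equal arms, a 100 g difference and SDs solved from 370, since none is stated.

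**What to change.** Rewrite the Sample size paragraph so that it carries one rule:

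- Remove the 2.5% as the multiplicity-adjusted level.
- State 0.05/3 = 0.0167 as the level for each intervention-versus-control test of birth weight, say whether it is one- or two-sided, and carry the same rule into the analysis plan.
- Give the SD used and restate the power at 370 per arm for that rule, even if it falls below 80%.

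Suggested content: each of the three comparisons with control is tested at [one- or two-sided] alpha 0.05/3 = 0.0167, holding the FWER at 0.05; with 370 evaluable women per arm, a 100 g difference and an SD of [value] g, power is [value]%.

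A two-sided test, or Dunnett's method in place of Bonferroni, is open to the investigators, but the contradiction does not require either.

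The cost is one paragraph, best settled before the allocation code is revealed. No extra enrolment is needed; the stated power may become less favourable.

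### Bonferroni at 0.017 is the only multiplicity method named for the three control comparisons; Holm would hold the same family-wise error rate with equal or higher power, most so if all three arms work

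*Protocol article*

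**What the plan says.** All the relevant figures are in the Sample size section of the protocol article.

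- **Family of tests:** "three comparisons between arms, i.e., intervention arms with control".
- **Error rate and power:** "In order to achieve a test power of 80% and maintain family-wise error rate (FWER) of 0.05".
- **Method and size:** "Bonferroni method for three comparisons, alpha of 0.017, and an estimated sample size of 370 pregnant women per arm was attained".
- **Effect:** "For birth weight (the primary outcome), it is assumed that the mean difference will be at least 100 g".
- **Which arms are expected to work:** "Improved perinatal outcomes are hypothesized with the supplement of BEP alone or co-administration of BEP supplement with azithromycin as well as with nicotinamide and choline".
- **A second statement of alpha:** "1-tailed hypothesis testing of birth weight as the primary outcome, a significance level of 2.5% to account for multiple comparisons". This is not reconciled with 0.017 or with the FWER of 0.05.

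The Statistical analysis section gives one-way ANOVA with baseline adjustment and no multiplicity procedure. The Trial design section gives 1:1:1:1 allocation, and all three comparisons use the same control arm.

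**The concern.** Bonferroni compares each p-value with FWER/3 whatever the other two comparisons show. Holm compares the smallest with FWER/3, the next with FWER/2 and the last with FWER, and stops at the first non-rejection. It controls the FWER strongly under any dependence between the tests, as Bonferroni does, and can only add rejections.

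The difference is largest when several effects are real, because each success relaxes the threshold for the next. That is the situation this protocol expects: BEP is given in all three intervention arms (Interventions section), and improvement is hypothesized in each. At stake is a real effect of one regimen being declared non-significant when the same data and the same FWER would support rejecting the null.

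**Working it through.** **Inputs.** From Sample size: FWER 0.05, three comparisons, power 80% (read as power per comparison), difference 100 g, 370 evaluable per arm. From Trial design: equal allocation. With equal arms and a shared control, any two of the three test statistics have correlation 0.5.

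**The plan's own figures.** 0.05/3 = 0.0167, which rounds to the stated 0.017. The sample size per arm is n = 2(SD × k/100)², with k = z(1−α) + z(0.80), or z(1−α/2) + z(0.80) if two-sided. No SD is given, so 370 cannot be checked independently. Solving for the SD at n = 370 gives:

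- two-sided 0.0167: k = 2.394 + 0.842 = 3.236, SD about 420 g; putting 420 back gives 2 × (4.20 × 3.236)² = 369.4, rounded up to 370;
- one-sided 0.017: SD about 459 g.

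Neither SD is in the document. The power comparison does not need one, because 80% power at the Bonferroni cut-off fixes the expected value of the test statistic at k.

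**Cut-offs in order (Bonferroni uses only the first).**

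- One-sided FWER 0.05: 2.128, 1.960, 1.645, with k = 2.128 + 0.842 = 2.970.
- Two-sided FWER 0.05, or one-sided FWER 0.025: 2.394, 2.241, 1.960, with k = 3.236.

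**Hand bound.** The most Holm can offer one arm is a test at the last cut-off. One-sided this gives Φ(2.970 − 1.645) = Φ(1.325) = 90.7%; two-sided, Φ(3.236 − 1.960) = Φ(1.276) = 89.9%. Holm's power must therefore lie between 80% and about 90%.

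**Simulation.** At least 1,000,000 draws of three normal statistics with correlation 0.5 and mean k × (true gain/100 g). Entries are one-sided / two-sided at FWER 0.05. Power is for a 100 g arm, except in the 70 g row.

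| True gains (g) | Bonferroni, per comparison | Holm, per comparison |
|---|---|---|
| 100, 100, 100 | 80.0% / 80.0% | 87.0% / 86.4% |
| 100, 100, 0 | 80.0% / 80.0% | 82.9% / 82.8% |
| 100, 50, 50 | 80.0% / 80.0% | 80.9% / 80.6% |
| 100, 0, 0 | 80.0% / 80.0% | 80.0% / 80.1% |
| 70, 70, 70 | 48.0% / 44.9% | 56.0% / 51.8% |

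With 100 g in every arm:

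- the chance of rejecting all three nulls rises from 61% to 78% (one-sided) or 77% (two-sided), so the chance of missing at least one real effect falls from 39% to 22–23%;
- the chance of rejecting at least one is 95.0% under both methods, because Holm's first step is the Bonferroni test.

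In every configuration with a true null, Holm's simulated FWER stayed at or below the nominal rate. Step-down Dunnett, which uses the 0.5 correlation, adds a little: 86.9–87.7% with all arms at 100 g and 81–82% with one effective arm.

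**The case against.** Bonferroni and 0.017 appear only as the basis of the sample size. The analysis section sets no decision rule, and the statistical analysis plan, which is not shown, may name one. Sizing at 0.05/3 is also exactly right for Holm's first step. This stands: a reader might infer that the protocol commits the final analysis to single-step Bonferroni, but the document does not say so. It only names no other method.

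Next, nothing here is invalid. Bonferroni holds the FWER, and 80% per comparison is the plan's own target. It also yields matching simultaneous confidence intervals for mean differences, which Holm does not do in a standard way. This stands too, so the point is about efficiency and does not show an error.

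Finally, a reader might take about 87% as the power that Holm delivers in general. The calculation does not support that. The figure needs all three arms to gain 100 g, which is the protocol's hypothesis but also the most favourable of the configurations examined at the design effect. Holm helps one comparison only after another has succeeded.

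What remains is that, for hypothesis testing, Holm is never worse than the one method the document names.

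**Conclusion.** The point holds as a recommended improvement with a conditional gain. At 370 evaluable women per arm, Holm adds about 6 to 7 percentage points of power per comparison and about 16 to 17 points to the chance of detecting all three effects, provided every arm gains 100 g. The gain is about 3 points with two effective arms, about 1 point for a 100 g arm beside two 50 g arms, and essentially nil with one effective arm.

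These figures assume that 80% means power per comparison under Bonferroni, that arms are equal in size so the correlation is 0.5, and that the test statistics are approximately normal. They do not depend on the unstated SD and change by less than one point between the one- and two-sided readings.

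The documents do not support saying that the trial is underpowered against its own target, or that its error control fails.

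**What to change.** Before unblinding, state in the protocol or analysis plan:

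1. The three birth-weight comparisons with control are tested by Holm at the adopted FWER: ordered p-values against FWER/3, FWER/2 and FWER, stopping at the first non-rejection.
2. Whether the p-values are one- or two-sided, reconciled with the one-tailed 2.5%, the 0.017 and the FWER of 0.05 in the Sample size section. Without this the rule cannot be applied: the cut-offs are 2.128/1.960/1.645 on one reading and 2.394/2.241/1.960 on the other.
3. 370 evaluable women per arm is kept, with 80% described as the minimum power per comparison at the design effect.
4. Holm-adjusted p-values are reported beside conventional or Bonferroni-level confidence intervals.

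If an existing analysis plan already names a step-down test, the protocol only needs to agree with it.

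The cost is a short text change with no effect on enrolment, treatment or data collection. The drawback is that simultaneous intervals matching a step-down test are less standard, so an interval may not always agree with its adjusted p-value.
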